### Sample Size Calculation

Statistical assumptions justifying our proposed total sample size of 450 patients (in total, including consenting patients from the original Toronto study as well as patients from all participating sites recruited in the multi-center study) are as follows, as they relate to the primary outcome analysis: i) Based on our current preliminary data from Toronto (September, 2020), the ratio of those choosing AS to those choosing surgery will be 3:1. ii) Based on published data from a prior published retrospective study of Toronto patients under the care of a primary investigator ([name]), it is expected that within an approximately 5-year time frame, approximately 3.4% of low risk papillary thyroid cancer patients in the surgical arm will receive treatment for recurrent disease (17). For purpose of sample size calculations this number is rounded down to 3%, in the time frame of about 2 to 3 years. Based on published data on active surveillance of VL-PTC, which is largely based on papillary microcarcinomas (7), we estimate that after about 2 - 3 years of follow-up, the cumulative incidence of disease progression requiring surgery in the AS arm will be approximately 3% (including both tumor growth and incident nodal metastatic disease). The sample size is guided by estimation of disease management ‘failure’ (absence of success) in the AS arm, as outcomes with surgery are better established. To estimate the risk of ‘failure’ of disease management in the AS group with an expected 95% confidence interval half-width of 2% (e.g., a confidence interval of 2% around the estimate of 3%), the required sample size is 328; there is an 80% chance the CI half-width will be narrower than 2.1%. Under the 3:1 ratio assumption above, approximately 110 surgical patients need to be recruited to obtain 328 AS patients. In order to accommodate some attrition in both groups, we plan to recruit a total of 450 patients (including patients consenting to long-term follow-up from the original Toronto study) and expect approximately 330 in AS group and 120 in the surgical group). Recruitment of surgical arm patients will enable controlled comparisons for the secondary outcomes. The sample size will be re-evaluated on a yearly basis, and the total sample size may be adjusted accordingly to maintain the desired precision in the AS arm.

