Recent literature suggests that AS of small, low risk PTC (confined to the thyroid), is safe (7). In a recent systematic review and meta-analysis of long-term outcomes of patients with small, low risk PTC under AS, Cho et al. reported that only 5.3% of patients experienced tumor growth ≥3 mm in maximal diameter and 1.6% of patients developed nodal metastases during 5 years of follow-up (7). No thyroid cancer-related deaths nor incident distant metastases have been observed in patients with small, low risk PTC under AS (8). However, most of the published literature on AS includes primarily patients with papillary microcarcinoma (PTC 1cm or smaller in largest diameter) (7), which may not routinely necessitate biopsy, per recent ATA clinical practice guidelines guidance (5). In 2016, in Toronto, we initiated a multi-phase prospective observational study of patients with small, low risk PTC < 2cm in maximal diameter (i.e. including PTC larger than microcarcinoma), which we refer to as very low risk PTC (VL-PTC) (9). In the Toronto study, we offer patients a choice of surgery or AS and report their disease management decision (decision-making phase of the study) (9). We also prospectively report patient outcomes in patients choosing AS or surgery (Clinicaltrials.gov: NCT03271892) (9). An interim analysis on the disease management decisions of the first 100 patients enrolled in the Toronto study was recently published (10). About half of the enrolled patients in the Toronto study have a PTC larger than a microcarcinoma (10). We reported that 71.0% (71/100) of our patients chose AS over surgery and patients’ rationale for the decision was described in detail using a qualitative approach (10). Although the high percentage selecting AS may in part reflect some referral bias (both self-referral of patients who are interested in AS and referral from thyroid cancer specialists whose patients specifically request AS), these preliminary data suggest that among Canadians with VL-PTC there is substantial interest in being offered the choice of AS as an alternative to surgery (10). One of the main reasons why our patients chose AS, was a desire to avoid immediate thyroid surgery, with the potential implications of thyroid hormone treatment (10). In contrast, patients who chose surgery wanted to remove any thyroid cancer in their body (i.e. aspired for cure of the disease). Recruitment in the Toronto prospective, observational AS decision-making study is now complete (200 patients), (with a full report on disease management decisions forthcoming). Furthermore, long-term patient follow-up is ongoing in the Toronto study. In response to a) popularity of the option of AS in patients with small, low risk PTC in the Toronto study (10), b) recently acquired knowledge in this area (in the published literature and clinical practice guidelines), and c) recent interest among Canadian thyroid cancer specialists, we have developed a prospective observational pan-Canadian study examining long-term clinical and patient-reported outcomes on AS and surgery for VL-PTC. The proposed study, described below, is similar to design to the original Toronto study, but with a focus on clinical outcomes and patient reported outcomes over a long period of follow-up.

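### No interval method tried gives both 328 AS patients and the 80% assurance, and the total of 450 leaves the AS arm almost no allowance for attrition

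*Protocol article*

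**What the plan says.** All the figures stand in one paragraph of the protocol article, Sample Size Calculation.

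- **Risk.** After about 2 to 3 years, "the cumulative incidence of disease progression requiring surgery in the AS arm will be approximately 3" per cent.
- **Precision target.** The AS failure risk is to be estimated "with an expected 95% confidence interval half-width of 2" per cent.
- **Size and assurance.** "the required sample size is 328; there is an 80% chance the CI half-width will be narrower than 2.1" per cent. No interval method is named.
- **Allocation.** From preliminary Toronto data of September 2020, "the ratio of those choosing AS to those choosing surgery will be 3:1", so that "approximately 110 surgical patients need to be recruited to obtain 328 AS patients".
- **Attrition.** "In order to accommodate some attrition in both groups, we plan to recruit a total of 450 patients". No loss rate is given.
- **Expected split.** The authors "expect approximately 330 in AS group and 120 in the surgical group".

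The paragraph also provides for yearly re-evaluation, with the total adjustable to keep AS precision. Under Statistical Analysis, the primary estimate is a Kaplan-Meier cumulative incidence with a 95% confidence interval; again the type of interval is not named.

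**The concern.** The sample size rests on the precision of the AS failure estimate alone; there is no hypothesis test behind it. The expected half-width, the number 328 and the 80% assurance are presented as properties of one design, so one interval method should produce all three. If none does, a reader cannot tell what precision was intended, and the yearly re-evaluation has no clear target.

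The attrition statement raises a similar doubt. The two expected arm sizes add up to 450, so they are numbers recruited, before any loss. The number expected in AS is almost the number required, although the total is said to have been raised to absorb losses in both arms.

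**Working it through.** **Inputs** (all from Sample Size Calculation): risk p = 3%, two-sided 95% interval, half-width 2%, n = 328, 80% chance below 2.1%, ratio 3:1, total 450, split 330/120.

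**1. Reproducing 328.** Let X ~ Binomial(n, 0.03) and half-width = (upper − lower)/2.

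- Continuity-corrected Wald at p = 3%: 1.96·√(0.03·0.97/n) + 1/(2n). At n = 327 this is 2.002%. At n = 328 it is 1.846% + 0.152% = 1.9985%. So 328 is the first n to reach 2%.
- Exact (Clopper-Pearson), averaged over X: first at or below 2% at n = 327; 1.994% at n = 328.
- Plain Wald at p = 3%: n = 1.96²·0.03·0.97/0.02² = 279.5, so 280; averaged over X, 271.

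The stated 328 therefore reproduces, by either of two routes.

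**2. Chance of a half-width below 2.1% at n = 328.** The half-width rises with X over the relevant range, so the chance is P(X ≤ k), with k the largest count whose half-width is below 2.1%. P(X ≤ 10) = 60.3%, P(X ≤ 11) = 71.7% and P(X ≤ 12) = 81.0%.

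| Interval | n for a 2% half-width (averaged over X; at p = 3%) | Mean half-width at 328 | Chance below 2.1% at 328 |
|---|---|---|---|
| Exact | 327; 334 | 1.99% | 60.3% |
| Wald, continuity-corrected | 320; 328 | 1.97% | 60.3% |
| Agresti-Coull | 320; 325 | 1.97% | 71.7% |
| Wilson | 296; 303 | 1.89% | 81.0% |
| Jeffreys | 279; 287 | 1.84% | 81.0% |
| Plain Wald | 271; 280 | 1.82% | 81.0% |

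The log-log interval needs 310 to 316 patients and gives 71.7%. Mid-p and likelihood-ratio intervals give 81.0% but need only 287 and 276 patients (averaged over X). No row gives both 328 and 80%.

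**3. What goes with 328.** At X = 11 the half-width is 2.118% (exact) or 2.101% (continuity-corrected). Counting it as 2.1% raises the chance to 71.7%, still short of 80%. At X = 12 it is 2.1995% or 2.184%, so for both intervals that give about 328, the chance of a half-width below 2.2% is 81.0%.

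**4. Attrition and split.**

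- Before attrition: 328/3 = 109.3, so about 110 surgical patients and 438 in all.
- The rise to 450 adds 12. AS gains 330 − 328 = 2 (2/330 = 0.6%); surgery gains 120 − 110 = 10.
- 330/120 = 2.75, not 3.
- At 3:1, 450 × 0.75 = 337.5 AS patients, a margin of 9 to 10 (9.5/337.5 = 2.8%).

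**5. Loss under the planned Kaplan-Meier analysis.** The article gives no loss rate, so the rates here are assumptions. In a simulation of 328 AS patients with 3% risk at 2.5 years, constant event and loss hazards and a plain Greenwood interval, the mean half-width is 1.82% with no loss, 1.87% with 10% loss and 1.92% with 20% loss. The chance below 2.1% is about 81%, 77% and 70%. With a log-log interval, the means are 1.94%, 1.99% and 2.06%, and the chances 72%, 64% and 54%.

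**The case against.** The strongest reply is that the design may well deliver what it promises. The planned estimator is Kaplan-Meier. With a plain Greenwood interval and no loss, 328 patients meet both targets: the expected half-width is 1.82% and the chance below 2.1% is 81%. This stands. A reader might infer from the 60% figure that the study falls short of its stated precision, but the 60% belongs to intervals that the article does not name, and it is sensitive to whether X = 11 counts. What the reply cannot rescue is the word required: under that interval, 2% needs about 271 to 280 patients, not 328.

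A reader might also take lost patients off the 330 and recompute a binomial interval, which makes the assurance look far worse. That is not the planned analysis. Kaplan-Meier keeps each patient at risk until loss, and the decline is milder, as the simulation shows.

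A third tempting step starts from the Introduction: "We reported that 71.0% (71/100) of our patients chose AS over surgery". At that share, 450 would give 450 × 0.71 = 319.5 AS patients, fewer than 328. But this is an interim result on the first 100 Toronto patients, while the 3:1 assumption cites Toronto data of September 2020. It does not contradict the plan.

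Finally, the split is worded as approximate, and the yearly re-evaluation may adjust the total. That softens the thin margin. It does not supply the allowance the paragraph claims, and it depends on a precision target that is stated inconsistently.

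**Conclusion.** The point holds as an inconsistency among stated figures. Among the intervals tried, those that give about 328 give a 60% chance of a half-width below 2.1% (72% with rounding) and reach 80% near 2.2%. Those that give about 80% need roughly 270 to 300 patients for a 2% half-width. Either the number or the assurance needs restating. This rests on p = 3% and on binomial enumeration at a fixed time; the article does not say which interval was used.

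The attrition statement fails on the article's own numbers, whatever the interval: 2 spare AS patients (0.6%) at the expected split, or 9 to 10 (2.8%) at 3:1, and the two splits do not agree.

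The documents do not show that the study will be too imprecise. The disputed gap in half-width is about 0.1 percentage point, and no test or decision threshold depends on it. Severity is minor to moderate.

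**What to change.** Reword the sample-size paragraph.

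1. Name the interval method and pair 328 with its own assurance. For the exact interval: 328 AS patients give an expected half-width of 2.0% and about an 80% chance that it is below 2.2%. For a plain Wald or Greenwood interval: 328 give about 1.8% and about an 80% chance below 2.1%, and 328 is more than a 2% half-width requires.
2. Replace the attrition claim with the real AS margin (about 2 patients at 330, 9 to 10 at 3:1), or state an assumed loss rate and the half-width expected under the planned Kaplan-Meier analysis.
3. Make the expected split agree with 3:1 (about 337 or 338 AS and 112 or 113 surgical), or explain why 330/120 is expected.
4. Use the restated figures as the target of the yearly re-evaluation.

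The cost is a few sentences. No extra patients are needed and the planned analysis does not change.

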### Statistical Analysis

Descriptive data will be presented in the surgical and AS groups for baseline demographic characteristics, medical history, initial disease management choice (surgery or AS), patients’ rationale for their choice, thyroid cancer treatments, and thyroid hormone treatment. Summaries of follow-up date will tabulate major complications of thyroid cancer surgery (i.e. clinically diagnosed hypoparathyroidism or recurrent laryngeal nerve injury beyond the first year after any thyroid cancer surgery), most recent PTC disease status, proportions crossing over from AS to surgery (and indication), and deaths (thyroid cancer-specific and overall, respectively).

The primary analysis will separately estimate the cumulative incidence of ‘failure’ of disease management (along with 95% confidence intervals) at any given time since enrolment in the AS and surgical arms, using the Kaplan-Meier method. The differences in cumulative incidence will also be calculated (with 95% confidence intervals).

For categorial outcomes, we will report proportions with 95% confidence intervals according to AS or surgical group. For all categorical clinical outcomes for which there is a sufficient number of events for meaningful analysis, we will compare the AS and surgical groups using competing risks models. We will summarize the following secondary patient-reported outcomes in each group: i) quality of life (thyroid cancer/cancer-specific) (12, 13), ii) anxiety (14), iii) survivor concerns (16), and iv) decision regret (15) (relating to the original decision on VL-PTC disease management). The data will be reported at last available study follow-up, with data from prior time points analyzed in interim analyses, if there are sufficient patients and events for meaningful analysis. All questionnaire data will be scored as per developers, for total scores or subscale scores. Where patient reported outcomes are missing and patients are known to be alive, multiple imputation will be used, with other outcomes one the same patient at the same time or other times in the imputation model. For each questionnaire outcome, we will calculate summary statistics to characterize the cohort at the last follow-up. Analyses will be adjusted for baseline variables, including age, sex, and primary tumor size (≤ 1cm or > 1cm) as well as duration of follow-up. If sufficient data are available for meaningful analysis will examine predictors of psychosocial health outcomes (e.g. age, sex, primary tumor size) if sufficient data are available for meaningful analysis. Clinical outcomes will also be compared between men and women, if there are sufficient events.

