### Study Aim and Primary Outcomes

Our primary research objective is to quantify the safety of AS relative to immediate surgery, by examining the rate of ‘failure’ of disease management over the period of follow-up in VL-PTC patients choosing AS and those choosing surgery. ‘Failure’ of disease management is defined as follows in each arm of the study: i) AS arm – thyroid surgery for progression of cancer, and ii) Surgical arm - surgery or other thyroid cancer treatments for structural disease recurrence or persistence at any time point after completion of initial treatment. Treatment of recurrent or persistent thyroid cancer (after completion of initial treatment) may include additional surgery, radioactive iodine treatment, ethanol ablation of lymph nodes, or external beam radiation treatment. Data will be reported separately for each arm.

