	•Patient is unable or unwilling to consent for study follow-up procedures (e.g. due to current severe active cognitive or psychiatric impairment, substance abuse, or other reasons)

*****Changes in the original Toronto protocol, approved by the University Health Network Research Ethics Board (April 7, 2020) and incorporated in the pan-Canadian at onset of the study include: not mandating central cytopathology review (i.e. may be performed at the discretion of the investigator if there is any uncertainty or concern about the original review, but not mandating this due to limited value with some patient delays observed in the Toronto study), not excluding patients who have mild thyroid or parathyroid disease that does not meet established absolute indications for surgical treatment (e.g. hyperthyroidism under control with medication, mild primary hyperparathyroidism), excluding patients with any prior thyroid surgery (not just thyroid cancer surgery, as prior partial thyroidectomy could confound results at long-term follow-up, although no patients with prior thyroid surgery have been enrolled in the Toronto study), and permitting patients who have had a recent diagnosis, treatment, or active surveillance of another malignancy to participate in the study if the expected survival of the other malignancy is > 1 year (as patients with other malignancies, including those under active surveillance for other low risk cancers, have expressed interest in this study).

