### Study Follow-Up Assessments and Outcomes

As in the original study (9), AS routine follow-up includes clinical assessment (comprised of neck ultrasound at the participating institution, bloodwork (TSH, thyroglobulin, thyroglobulin antibody), and investigator clinical evaluation) every 6 months for two years, then yearly if there has been no evidence of disease progression. More frequent assessments or additional investigations may be performed if there is a clinical concern. Indefinite clinical follow-up at a participating study site is offered for patients as long as they are undergoing AS. The criteria for recommending surgery for disease progression (the same as in the original study) are defined as any of: 1) primary tumor growth > 3mm (in largest diameter, confirmed on two consecutive ultrasound exams); 2) PTC growth in a location that is concerning (i.e. encroaching the trachea or course of the recurrent laryngeal nerve or grossly invading extrathyroidal tissues); or 3) incident nodal metastatic disease, or 4) incident distant metastatic disease (**Table 2**) (9). Furthermore, as in the original Toronto study, patients under AS are free to choose to cross over to surgery in the absence of disease progression at any point in follow-up and may continue to be followed in the study (in a manner analogous to that of patients who choose immediate surgery) (9). In patients initially choosing surgery or crossing over from AS to surgery, the extent of surgery and any other treatments will be at the discretion of the treating surgeon or thyroid cancer specialists (who are not mandated to be at a participating study site), and is intended to reflect usual care. Typical post-surgical disease surveillance of patients treated for VL-PTC includes periodic clinical evaluations, neck ultrasounds, and bloodwork (TSH, thyroglobulin, thyroglobulin antibody), with additional investigations considered depending on the clinical circumstance. In the event that the clinical criteria for salvage surgery are met, it is expected that the treating or referring surgeon will perform thyroid surgery, but the patient may opt for a surgeon of her or his choice at any institution (usual care). Although highly unlikely, it is possible that a patient may decline surgery (e.g. due to development of new co-morbidity, or other reasons). Any occurrence of non-compliance with a recommendation for salvage surgery will be recorded, including the reason. However, based on our experience in Toronto, although sometimes patients may delay recommended surgery (e.g. due to life circumstances or COVID-19 pandemic related reasons), we have not had any patient completely refuse surgery and to date, ultimately all patients who were advised to have surgery by study investigators have done so. In the case of patients who initially decline surgery, close AS follow-up will continue, with imaging and clinical follow-up frequency per discretion of the study investigator (typically 3 to 6 months).

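### The primary cumulative incidence of failure is to be estimated by Kaplan-Meier although elective surgery and death preclude failure; long-term risk is overstated, mainly in the AS arm

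*Protocol article*

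**What the plan says.** All references are to the protocol article.

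- **Target and estimator (Statistical Analysis).** "The primary analysis will separately estimate the cumulative incidence of ‘failure’ of disease management", with 95% confidence intervals, "at any given time since enrolment in the AS and surgical arms, using the Kaplan-Meier method". The difference in cumulative incidence between the arms is also to be calculated.
- **Failure in the AS arm (Study Aim and Primary Outcomes).** "AS arm – thyroid surgery for progression of cancer". Surgery for any other reason does not count.
- **Elective crossover (Study Follow-Up Assessments and Outcomes).** "patients under AS are free to choose to cross over to surgery in the absence of disease progression at any point in follow-up". Such patients "may continue to be followed in the study (in a manner analogous to that of patients who choose immediate surgery".
- **Reporting of crossover and death (Statistical Analysis).** The follow-up summaries tabulate "proportions crossing over from AS to surgery (and indication), and deaths (thyroid cancer-specific and overall, respectively". Nothing ties these tabulations to the primary curve.
- **Competing risks elsewhere (Statistical Analysis).** For categorical clinical outcomes with enough events, "we will compare the AS and surgical groups using competing risks models".
- **Eligibility (Table 1 footnote).** Patients with another malignancy may enter "if the expected survival of the other malignancy is > 1 year".
- **Horizon (Study Follow-Up Assessments and Outcomes, after Table 2).** Records are reviewed for up to 10 years.

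**The concern.** Elective thyroid surgery ends surveillance of the index tumour, so the AS failure event as defined can no longer occur. Death has the same effect in either arm. Both are competing events, not incomplete observation. Kaplan-Meier in its standard form treats them as censoring and in effect lets censored patients go on to fail at the rate of those still at risk. The result is not the cumulative incidence that the plan names.

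The AS failure risk is the study's main number, and the article's Discussion expects the results to inform patient counselling. An overstatement that grows with follow-up falls on the long-term estimates. It also enters the planned difference unequally, because one of the two competing events exists in one arm only. The plan brings in competing-risks models for between-group comparisons, yet fixes a different method for the primary curves.

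**Working it through.** **1. The plan's own figure.** Sample Size Calculation gives 328 AS patients for a 95% half-width of 2 points around 3%. Continuity-corrected Wald: 1.96 × √(0.03 × 0.97 / 328) + 1/(2 × 328) = 1.85 + 0.15 = 2.00 points. The expected Clopper-Pearson half-width at 328 is 1.994 points. The figure reproduces, and nothing below changes it.

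**2. Inputs.**
- AS failure risk: 3% at about 2 to 3 years (Sample Size Calculation), taken here as 2.5 years.
- Competing events (elective surgery plus death): no rate is given. **Assumed** 0.5% to 10% per year.
- **Assumed** constant hazards, with competing events independent of failure.

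**3. Formulas.**
- Failure hazard: h₁ = −ln(0.97)/2.5 = 0.01218 per year.
- Competing hazard: h₂ = −ln(1 − c), with c the assumed yearly rate.
- 1-KM = 1 − exp(−h₁t).
- Cumulative incidence = h₁/(h₁ + h₂) × [1 − exp(−(h₁ + h₂)t)], which the Aalen-Johansen method estimates.

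Example, c = 5% and t = 10: h₂ = 0.05129 and h₁ + h₂ = 0.06348. Cumulative incidence = 0.1919 × (1 − 0.5301) = 9.02%. 1-KM = 1 − exp(−0.1218) = 11.47%. The gap is 2.45 points.

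**4. Results** (cumulative incidence in %, gap in percentage points in brackets).

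| Assumed competing rate per year | 2.5 years (1-KM 3.00) | 5 years (1-KM 5.91) | 10 years (1-KM 11.47) |
|---|---|---|---|
| 0.5% | 2.98 (0.02) | 5.84 (0.07) | 11.19 (0.28) |
| 1% | 2.96 (0.04) | 5.77 (0.14) | 10.92 (0.55) |
| 3% | 2.89 (0.11) | 5.49 (0.42) | 9.92 (1.55) |
| 5% | 2.82 (0.18) | 5.22 (0.69) | 9.02 (2.45) |
| 10% | 2.64 (0.36) | 4.61 (1.30) | 7.17 (4.31) |

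The last row is extreme: 62% of patients would have had a competing event by 10 years. At 3% and 5% per year the figures are 25% and 38%.

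**5. Against sampling error.** The planned 2 points belong to a 3% risk. At 10 years, with 328 patients fully followed, the plain Wald half-width at 11.47% is 1.96 × √(0.1147 × 0.8853 / 328) = 3.4 points. A gap of 2.45 points is therefore below one half-width but, unlike sampling error, always has the same sign.

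**6. The difference.** Suppose both arms have the same failure hazard, with competing rates of 3% per year under AS and 0.5% (death only) after surgery. At 10 years the Kaplan-Meier difference is 11.47 − 11.47 = 0. The actual difference is 9.92 − 11.19 = −1.27 points in favour of AS.

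**7. If crossover depends on progression risk.** A simulation of 2,000,000 patients, with failure risk varying between patients and crossover at about 3% per year, gave at 10 years (true net risk, had nobody crossed over, 10.9%):

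| Relation of crossover to progression risk | 1-KM | Cumulative incidence |
|---|---|---|
| Positive | 9.7% | 8.5% |
| None | 10.9% | 9.4% |
| Negative | 11.6% | 10.1% |

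1-KM lies above the cumulative incidence in every row. It matches the net risk only when crossover is independent of progression risk.

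**The case against.** **Net risk may be the intended target.** The aim is the safety of AS, and the risk of progression surgery among those who remain on AS is a defensible quantity. The crude risk falls as more patients leave electively, which can flatter AS. This stands as a reason to show both, but the plan names cumulative incidence, not net risk.

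**Informative censoring.** A reader might infer that patients with early growth or worry are the ones who cross over, and that this adds to an upward bias. The documents give reasons for the initial choice between AS and surgery, not for later crossover. The link is plausible but undocumented. If it held, 1-KM would be too low for net risk (9.7% against 10.9% above) while still too high for cumulative incidence. The two effects do not add up to one upward bias.

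**Competing-risks models may already cover failure.** The sentence refers to all categorical clinical outcomes, so failure may be included in the between-group model. That would leave the arm-specific Kaplan-Meier curves, and the difference calculated alongside them, as they are.

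**The censoring rule is not written out.** This is true. Keeping crossovers and deaths in the risk set up to the data cut-off would recover the cumulative incidence. That is not standard Kaplan-Meier, and the text does not describe it.

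**Size.** A reader might set the 10-year gap against the planned 2 points and call the primary result invalid. That margin applies to a 3% risk, the competing rates are assumed, and at 2 to 3 years the gap is trivial. This part of the objection stands in full.

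**Conclusion.** The point holds. The estimator fixed for the primary outcome does not estimate the quantity named when elective surgery and death are censored. 1-KM cannot fall below the actual cumulative incidence, and it exceeds it once failures occur after competing events. If failure hazards and mortality are broadly similar in the two arms, the excess is larger under AS and the difference is biased against AS.

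The size cannot be fixed from the document. It depends on the planning risk of 3% at 2.5 years, constant hazards and assumed competing rates. On that basis the matter is one for the long-term estimates and not for the 2 to 3 year horizon used for planning. Read instead as the net risk of staying on AS, Kaplan-Meier is valid only if crossover is independent of progression risk; the document supports neither independence nor a direction of dependence.

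**What to change.** In Statistical Analysis, replace the primary estimator with the Aalen-Johansen cumulative incidence in both arms, and take the difference and its confidence interval from it. Competing events: thyroidectomy without progression (AS arm only) and death without failure (both arms). Show the cumulative incidence of elective surgery beside the AS failure curve. Keep Kaplan-Meier as a sensitivity analysis, labelled as net risk under independent crossover.

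The cost is a few lines of text and a different software call. Crossover indication and deaths are already to be tabulated, so no new data are needed; their dates must be available for the analysis. The downside is that the crude failure risk depends on how many patients leave AS electively, so the two curves must be read together.
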